[12]. PET-MRI appears to offer higher lesion conspicuity and diagnostic confidence compared to PET-CT
[13], and this additional information can influence clinical management of cancer patients The combined advantages of detection of smaller hepatic tumours with a higher sensitivity and detection of focal FDG uptake suggestive for LTP indicates that PET-MRI could provide complementary information and facilitate improved clinical decision making
[14].

To the best of our knowledge, the effectiveness of integrated PET-MRI in RFA or MWA follow-up has not been investigated. The primary aim of this study is therefore to determine the accuracy of 18 F-FDG PET-MRI in LTP detection. Secondary aims will be to investigate whether PET-MRI is more accurate than PET-CT and ceCT in the detection of new intra-hepatic lesions, and to evaluate inter-observer variability, the impact of PET-MRI on future treatment and patients’ views on both modalities. We hypothesize that PET-MRI will be at least equivalent to PET-CT in the diagnosis of LTP, but superior to PET-CT in the early detection of new intrahepatic lesions and therefore able to positively influence decision making in patients with RFA/MWA-treated CRLM.

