### Image analysis

Only PET-CT and 4-phase liver CT images will be analysed and used in the context of routine patient care during clinical follow-up. The PET-MRI images will not be part of the diagnostic and follow-up process.

For imaging analysis, blinded data sets of all scans will be viewed both separately and independently by two designated, experienced radiologists and two nuclear medicine physicians. The reviewers will be blinded to the results of the other imaging modalities and to final patient outcome. A time-interval of at least four weeks will be introduced between the first and second review. Progressive disease will be scored on a per-patient and per-lesion basis, and results of all imaging modalities will be compared. The criteria for progression on different modalities are defined in Table 
3. Each lesion on each modality will be scored on a separate form and results will be scored from 1–5 (Table 
4) and size and location of the lesions will be reported. A LTP is defined as a lesion located in or within 1 cm of the ablation zone; a new intrahepatic lesion is defined as a lesion located more than 1 cm distant from the ablation zone
[6]. On MRI, a suspicious lesions has to meet the definition of LTP in at least two different sequences before it is considered positive for progression.

**Table 3 T3:** Test positivity criteria for progressive disease on different imaging modalities; ≤1 cm of the ablation zone (LTP) / >1 cm of the ablation zone (new intrahepatic recurrence)

ceCT		Newly detectable hypodense lesion
MRI	T1	New focal hypo-intense lesion
	T2	New focal hyper-intense lesion
	Contrast enhanced	Irregular peripheral enhancement pattern of a circumscribed lesion
	Diffusion weighed	Lesion with high signal intensity on b800
FDG PET		Lesion with clearly increased focal uptake as compared to liver background

**Table 4 T4:** Study form for reviewers’ results (per lesion base)

**Study number:**		**Reviewer number:**
**Score**	**Definition**	**Explanation**
1	Normal	Confident that no tumor recurrence is present in the ablation zone/confident that no new intrahepatic lesions are present
2	Probably benign	The appearance of the ablated lesion is compatible with post-ablational inflammation or rim-like characteristics/the new lesions diagnosed do not appear malignant

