3	Equivocal	There is doubt whether the enhanced FDG, CT- and/or MRI features indicate tumor progression or inflammation/there is doubt whether the new lesions diagnosed are benign or malignant
4	Probably malignant	Confident of local progression in the ablation zone/confident of new intrahepatic metastases
		Size or estimated size:
		Location:
		Intensity FDG vs normal liver; slight/moderate/intense
5	Impaired quality	Quality of the images precludes adequate diagnosis
Comments:		

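### Score 4 on the reader form, the only malignant grade, has a label and an explanation that set different levels of certainty

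*Protocol article*

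**What the plan says.** The Image analysis section of the protocol article describes the instrument: "Each lesion on each modality will be scored on a separate form and results will be scored from 1–5". Table 4 gives each score a short label in a definition column and a fuller text in an explanation column.

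- Score 1, normal, is explained as "Confident that no tumor recurrence is present in the ablation zone/confident that no new intrahepatic lesions are present".
- Score 2 is labelled "Probably benign". Its explanation describes benign-looking appearances and does not speak of confidence.
- Score 3, equivocal, is explained by doubt: "There is doubt whether the enhanced FDG, CT- and/or MRI features indicate tumor progression or inflammation", with parallel wording for new lesions.
- Score 4 is labelled "Probably malignant" and explained as "Confident of local progression in the ablation zone/confident of new intrahepatic metastases".
- Score 5 records that image quality is too poor for a diagnosis.

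Two radiologists and two nuclear medicine physicians read the scans independently. Inter-observer variation is a secondary outcome (Primary and secondary objectives). It is to be quantified with Cohen's kappa and proportions of specific agreement (Statistical analysis). Table 3 separately lists test positivity criteria for each modality.

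**The concern.** Being confident and thinking something probable are different states of mind, and the form itself treats them so on the benign side, where they have separate grades (1 and 2). On the malignant side both share one row. A reader who favours progression but keeps some doubt has two defensible scores. The Background says that, without proof of growth, CT and MRI cannot separate reactive tissue around the ablated lesion from viable tumour, so such lesions are to be expected in this trial.

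What is at stake is the agreement analysis. If readers settle on different columns, disagreement produced by the form will be reported as disagreement about the images. The form does not record which threshold a reader used, so this could not be separated out afterwards without a new read.

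**Working it through.** **1. Is the conflict real, or a damaged table?** The text gives a scale from 1 to 5, and all five rows are present. No row for certain malignancy has been lost. Score 5 is a quality code, so score 4 is the only malignant grade.

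**2. Where does each kind of lesion go?**

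| Reader's judgement | By label | By explanation |
|---|---|---|
| Confident of progression | 4 | 4 |
| Progression likely, some doubt | 4 | 3 |
| Cannot say either way | 3 | 3 |

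Only the middle line differs. Nothing elsewhere in the article says which column decides.

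**3. The plan's own figure.** The Sample size calculation uses n = 20 and p = 0.35. The exact binomial chance of at least 5 events is 0.8818, which reproduces the stated 88%. The present point does not depend on that figure. The same inputs give an expected count of 20 × 0.35 = 7, which serves as the count of malignant calls below.

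**4. Illustration of the effect on kappa.** These are assumptions, not figures from the article:
- There are 20 lesions, one binary call per lesion, with score 4 against the rest.
- Reader A follows the label and calls 7 malignant.
- Reader B sees exactly the same but follows the explanation, and so gives k of those 7 a score of 3.
- Both readers agree on the other 13.

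Observed agreement is (20 − k)/20. Chance agreement is [7(7 − k) + 13(13 + k)]/400. Kappa is (observed − chance)/(1 − chance).

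| k | Observed | Chance | Kappa |
|---|---|---|---|
| 0 | 1.00 | (49 + 169)/400 = 0.545 | 1.00 |
| 1 | 0.95 | (42 + 182)/400 = 0.560 | 0.39/0.44 = 0.89 |
| 2 | 0.90 | (35 + 195)/400 = 0.575 | 0.325/0.425 = 0.76 |
| 3 | 0.85 | (28 + 208)/400 = 0.590 | 0.26/0.41 = 0.63 |

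The proportion of specific agreement on malignant calls, 2(7 − k)/[2(7 − k) + k], falls in the same way: 12/13 = 0.92, 10/12 = 0.83 and 8/11 = 0.73.

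**5. Sensitivity, under a further condition.** If score 4 were the test-positive call and all 7 lesions were true progressions, reader A would have 7/7 and reader B 6/7 = 86%, 5/7 = 71% or 4/7 = 57%. The article does not state that condition.

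**The case against.** The explanations alone form a usable boundary: doubt goes to 3 and confidence to 4. Readers see both columns on one line, and an explanation is naturally read as instruction on how to use a short label. The word probably may only acknowledge that imaging is not histology. This stands in part. Experienced readers may well converge, and the illustration is a worst case because each reader follows one column on every borderline lesion. But the article does not secure that convergence, and the form's own separation of scores 1 and 2 argues against treating the two words as equivalent.

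A reader might infer more than the documents support:

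- **That the wording changes diagnostic accuracy.** No score is named as test-positive, and Image analysis places the criteria for progression in Table 3, with a rule for MRI of at least two sequences. If Table 3 decides positivity, the boundary between 3 and 4 leaves sensitivity untouched.
- **That specificity shifts.** The illustration keeps all 13 negatives concordant, so it shows no such effect.
- **That one modality is favoured.** The same form serves every modality, and a reader who applies one interpretation consistently applies it to all of them. No mechanism for a difference is shown.
- **That the form fails to measure a trial outcome by not separating probable from certain malignancy.** The remark that "PET-MRI appears to offer higher lesion conspicuity and diagnostic confidence compared to PET-CT" is background from a cited study. Diagnostic confidence is not among the listed outcomes, and a scale with fewer malignant than benign grades is a permissible choice.

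**Conclusion.** The point holds as an internal contradiction in one row of the reader form. Score 4 carries two certainty thresholds, and the article does not say which applies. The direct consequence is for inter-observer agreement, a stated secondary outcome, provided that the scores are what kappa compares. The illustrative fall from 1.00 to 0.89, 0.76 or 0.63 rests on assumed counts and on two readers holding to different columns throughout. It shows the scale of what could happen and does not forecast it. An effect on sensitivity is conditional on score 4 being the positive call. Effects on specificity or between modalities are not established. The row should be corrected before reading begins, because the ambiguity cannot be removed later without re-reading the scans.

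**What to change.** Before the first read, do one of the following:

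- make the label and explanation of score 4 express a single threshold, and adjust score 3 so that the two grades meet without overlap; or
- split the grade into 4 = probably malignant (findings favour progression, not certain) and 5 = malignant (confident of progression), and record inadequate image quality in a separate box.

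In either case, state which scores count as a malignant call and how that call relates to the positivity criteria in Table 3, including the two-sequence rule for MRI. The first option is the minimum, and the second is a matter of preference.

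The cost is a revised form and a short briefing of the four readers. No extra scans, patients or readers are needed.

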### Recurrent disease and repeated treatment

If recurrent disease is suspected on either 4-phase CT of the liver or on PET-CT, the patient will be evaluated for re-treatment by our multidisciplinary liver board. If either resection of a LTP or chemotherapy is indicated, the patient will be excluded from further participation in the study. If patients are eligible for repeated RFA/MWA treatment of the LTP, study participation will be continued. Patients with new intrahepatic lesions that are eligible for local treatment (surgery or ablation) will remain in the study, as long as the initially ablated area remains unaffected (Figure 
1). Prior to re-treatment with RFA/MWA, several biopsies will be taken from the suspected area for pathological confirmation. To minimize the chance of ‘track seeding’, tract ablation will be performed after the procedure. Extra-hepatic disease will be treated as deemed suitable. If there is any doubt as to whether an imaging feature indicates recurrent disease, the scan will be repeated after 3 months as a confirmation.

### Sample size calculation

Sample size estimates are based on the incidence of local site recurrences and new intrahepatic metastases. Previous studies have shown that 25-40% of the patients treated with RFA/MWA develop LTP, of which >95% occur within the first year
[4]. In addition, 30-40% of the patients will develop new intrahepatic metastases
[2,21]. At least 5 LTP and 5 new intrahepatic lesions are necessary for a meaningful comparison between PET-CT and PET-MRI in this observational study. Using the binominal distribution (with *p* = 0.35 and n = 20), the chance of finding 5 LTP and the chance of finding 5 new intrahepatic lesions in our population are both 88%. This suggests that the study has a satisfactory chance of success with a sample size of 20 patients. Patients excluded during the study period will be replaced by new participants, so that 20 patients will have completed one year follow-up at study completion.

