### Statistical analysis

We will determine the accuracy of PET-MRI for diagnosing recurrent disease compared to each imaging method (MRI, CT and PET-CT) and compared to pathology or clinical follow-up. Continuous variables will be summarized with standard descriptive statistics including means, standard deviations, medians and ranges when indicated. Categorical variables will be summarized with frequencies. McNemar’s test is used to determine agreement between PET-MRI and other modalities. The inter-observer variability will be quantified with Cohen’s Kappa and proportions of specific agreement. P-values less than 0.05 will be considered statistically significant. Statistical analysis will be performed using SPSS version 20.0 (SPSS Inc, Chicago).

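### The minimum of 5 events is not tied to the planned test: for sensitivity, 5 cases cannot reach p < 0.05 with a two-sided exact McNemar test

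*Protocol article*

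**What the plan says.** Under Sample size calculation, the article bases the number of patients on how often recurrence is expected. It cites that "25-40% of the patients treated with RFA/MWA develop LTP" and that "30-40% of the patients will develop new intrahepatic metastases". It then sets the requirement: "At least 5 LTP and 5 new intrahepatic lesions are necessary for a meaningful comparison between PET-CT and PET-MRI in this observational study". The calculation is given as "Using the binominal distribution (with *p* = 0.35 and n = 20"), with the result that "the chance of finding 5 LTP and the chance of finding 5 new intrahepatic lesions in our population are both 88" per cent. The conclusion drawn is: "This suggests that the study has a satisfactory chance of success with a sample size of 20 patients".

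Under Statistical analysis, the only test named for comparing modalities is McNemar's: "McNemar’s test is used to determine agreement between PET-MRI and other modalities". The threshold is fixed: "P-values less than 0.05 will be considered statistically significant". The section does not say whether the test is exact or asymptotic, one- or two-sided, or which pairs enter it.

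The Background hypothesises that PET-MRI is at least equivalent to PET-CT for local tumour progression (LTP) and superior for early detection of new intrahepatic lesions.

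**The concern.** The sample-size paragraph makes 5 events of each kind the condition for a useful comparison of PET-CT with PET-MRI. The analysis paragraph makes that comparison with McNemar's test at 0.05. McNemar's test uses only discordant pairs, and sensitivity is compared only in patients or lesions that truly have recurrence. With 5 such cases there can be at most 5 discordant pairs, which is too few for the usual small-sample form of the test to reach 0.05.

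If that is right, the stated chance of success says nothing about whether the named analysis can separate the two modalities. A non-significant result, likely unless the sensitivities differ greatly, could then be misread in two ways: as support for equivalence in LTP, or as evidence against superiority for new lesions. It would justify neither.

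**Working it through.** **Inputs.** From Sample size calculation: n = 20, event probability 0.35, minimum 5 events, ranges 25–40% (LTP) and 30–40% (new lesions). From Statistical analysis: McNemar's test, threshold 0.05. From Background: sensitivities 93% and 76% for hepatic metastases with post hoc fused images; the plan does not use them for sizing, so they serve here only as an illustration. Assumptions: two-sided testing, and pairs restricted to reference-positive cases, which is what a sensitivity comparison requires.

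**1. The plan's figure.** For X ~ Bin(20, 0.35), P(X ≥ 5) = 0.882, which reproduces the stated 88%. P(X = 5) is 0.127, so the article means at least 5.

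**2. Smallest attainable p with 5 cases.** Suppose all 5 are discordant in one direction (one modality finds all, the other none).
- Exact, two-sided: 2 × 0.5^5 = 0.0625.
- Chi-square with continuity correction: (5 − 1)²/5 = 3.2, p = 0.074.
- Chi-square without correction: 5²/5 = 5.0, p = 0.025.
- Exact one-sided, or two-sided mid-p: 0.5^5 = 0.031.

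**3. Smallest count that can reach 0.05.** With 6 cases, all discordant one way, the two-sided exact p is 2 × 0.5^6 = 0.031 (continuity-corrected 0.041). With 6, 7 or 8 discordant cases, every one must go the same way. A single case in the other direction is tolerated only from 9 discordant cases (p = 0.039).

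**4. Chance of having at least 6 events, n = 20.**

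| Event rate | P(at least 5) | P(at least 6) |
|---|---|---|
| 0.25 | 58.5% | 38.3% |
| 0.30 | 76.2% | 58.4% |
| 0.35 | 88.2% | 75.5% |
| 0.40 | 94.9% | 87.4% |

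Having 6 events makes a significant result possible, not probable.

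**5. Illustrative power.** With detection independent given disease, the probability that only PET-MRI detects a case is 0.93 × 0.24 = 0.223, and that only PET-CT does is 0.07 × 0.76 = 0.053. Two-sided exact power is 0 at 5 events, 0.07% at the expected 7 (20 × 0.35), and 0.26% averaged over Bin(20, 0.35). For the uncorrected chi-square the figures are 1.0%, 4.0% and 4.8%.

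Power depends on the assumed difference. Averaged over the same event distribution, again with independence:

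| Sensitivities | Exact | Uncorrected |
|---|---|---|
| 93% vs 76% | 0.3% | 5% |
| 95% vs 50% | 9% | 37% |
| 95% vs 30% | 29% | 66% |
| 100% vs 20% | 50% | 85% |

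**6. What 5 events support as estimation.** When all k cases are detected, the lower limit of the exact 95% interval for sensitivity is 0.025^(1/k). That gives 48–100% at 5/5 and 59–100% at 7/7.

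**The case against.** Several points can be made for the plan, and most of them limit the criticism.

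- **The test is not specified as exact or two-sided.** This stands. A reader might infer that 5 events can never be significant under the plan's own test. The article does not support that: the uncorrected chi-square gives 0.025 at 5 one-way pairs. That approximation is unreliable with so few pairs, but the statement must name the test variant.
- **The article uses McNemar's test for agreement, per patient and per lesion.** This also stands. False positives in patients or lesions without recurrence add discordant pairs, so 5 events do not cap the pairs in every McNemar analysis. The cap holds for sensitivity. Yet true recurrences are what the sample-size paragraph counts, and sensitivity is what they inform.
- **Five is a minimum.** Seven events are expected, and one patient may contribute several lesions. True, but the article makes 5 its criterion for an adequate comparison, and the illustrative exact power at 7 is still below 0.1%.
- **The article promises a meaningful comparison in an observational study, not a significant one, and no power is claimed.** Fair: the 88% is correctly calculated, and the fault is in the justification. But the article fixes a significance threshold, hypothesises superiority for new lesions, and gives no precision target that would lend the word another meaning.

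A reader might also infer that a non-significant result is certain whatever the true sensitivities. The calculations do not support this: averaged exact power reaches 50% at 100% vs 20%.

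**Conclusion.** The point holds in a limited form. For the sensitivity comparison, the planning minimum of 5 LTP or 5 new lesions cannot reach p < 0.05 with a two-sided exact McNemar test (minimum 0.0625) or with the continuity-corrected version (0.074). Six one-way discordant cases are needed, and the chance of even having 6 events is 75.5% at the plan's rate, against the 88% quoted for 5. The 5-event target is therefore not linked to the planned test, and the claimed adequacy is missing at the plan's own threshold.

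This rests on two-sided testing, a small-sample form of McNemar's test, and pairs limited to reference-positive cases. The power figures further assume independent detection and, for 93% vs 76%, sensitivities borrowed from a different setting. They show that power is very low for a difference of that size and substantial only for very large ones.

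**What to change.** **Sample size calculation.** State that 88% is the probability of observing at least 5 events of a given kind. Replace the claims of a meaningful comparison and of a satisfactory chance of success with an estimation statement, for example that the exact 95% confidence interval for sensitivity would be 48–100% at 5/5 and 59–100% at 7/7.

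**Statistical analysis.** Make the primary output sensitivity and specificity with exact 95% confidence intervals, together with the paired PET-MRI minus PET-CT difference and its interval. Label McNemar p-values as descriptive. Add that a non-significant McNemar result does not show equivalence.

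**Cost.** Rewording of two sections, with no extra patients or scans. The stated chance of success becomes less favourable, and the study is presented as estimation rather than as a test between modalities.

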### Statistical analysis

We will determine the accuracy of PET-MRI for diagnosing recurrent disease compared to each imaging method (MRI, CT and PET-CT) and compared to pathology or clinical follow-up. Continuous variables will be summarized with standard descriptive statistics including means, standard deviations, medians and ranges when indicated. Categorical variables will be summarized with frequencies. McNemar’s test is used to determine agreement between PET-MRI and other modalities. The inter-observer variability will be quantified with Cohen’s Kappa and proportions of specific agreement. P-values less than 0.05 will be considered statistically significant. Statistical analysis will be performed using SPSS version 20.0 (SPSS Inc, Chicago).

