## Abstract

**Background:**

Thermal ablation of colorectal liver metastases (CRLM) may result in local progression, which generally appear within a year of treatment. As the timely diagnosis of this progression allows potentially curative local treatment, an optimal follow-up imaging strategy is essential. PET-MRI is a one potential imaging modality, combining the advantages of PET and MRI. The aim of this study is evaluate fluorine-18 deoxyglucose positron emission tomography (FDG) PET-MRI as a modality for detection of local tumor progression during the first year following thermal ablation, as compared to the current standard, FDG PET-CT. The ability of FDG PET-MRI to detect new intrahepatic lesions, and the extent to which FDG PET-MRI alters clinical management, inter-observer variability and patient preference will also be included as secondary outcomes.

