### Primary and secondary objectives

We will assess the effectiveness of FDG PET-MRI in the follow-up of thermal ablation (RFA/MWA) of CRLM. Our primary aim will be to assess the accuracy of FDG PET-MRI in the diagnosis of local progression in the first year after RFA/MWA of CRLM. Therefore, all FDG PET-MRI images will be compared to FDG PET-CT and 4-phase liver CT images, which are the current standard of care. Results of different imaging sets will be compared on a per-patient and a per-lesion base. These results will then be compared to a reference standard: either histological outcome (if available) or clinical follow-up.

Secondary outcomes will include the accuracy of diagnosis of new intrahepatic disease after RFA/MWA. Since only a single 18 F-FDG per combined PET-MRI and PET-CT visit will be applied, we will have the opportunity to investigate whether dual-time point PET can increase the specificity of the 18 F-FDG signal and increase diagnostic accuracy
[15]. The reproducibly and robustness of inter-observer variation will also be determined. Clinical relevance will be studied by recruiting a panel consisting of a radiologist, interventional radiologist, nuclear medicine physician, oncologist, oncological surgeon and a radiation oncologist to retrospectively review PET-MRI images and agree on the preferred treatment. Choice of treatment based on PET-MRI will then be compared to the treatment that was actually received based on PET-CT and 4-phase liver CT. Finally, patients’ preferences will be assessed at one year follow-up using a specifically designed questionnaire that compares both modalities (Table 
1).

**Table 1 T1:** Questionnaire comparing PET-CT and PET-MRI (completed following fourth PET-MRI)

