### Study procedure

The standard follow-up protocol during the first year after RFA/MWA of CRLM in the VU University Medical Center consists of three-monthly whole-body FDG PET-CT and 4-phase liver CT, in combination with measurement of serum carcinoembryonic antigen (only when elevated pre-operatively). For the purposes of this study, liver FDG PET-MRI will be added to the routine procedure, using a 3.0 Tesla Ingenuity TF Philips scanner (Philips Medical Systems, Cleveland, OH). This hybrid PET-MRI system is characterized by a sequential acquisition mode and has separate scanners with a turntable patient handling system facilitating patient motion between the MRI and the PET gantries that are located at a 3 meter distance from each other.At the end of one year follow-up, patients will be asked to complete a questionnaire evaluating their experience with the PET-MRI compared to the PET-CT. The study procedure is illustrated in Figure 
1.

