The period between FDG injection and acquisition of the PET-CT in this study is 30 minutes longer than the standard protocol, which might increase our ability to detect intrahepatic malignancies. Background activity in the normal liver parenchyma due to high glucose metabolism and abundant expression of Glut-1 and Hexokinase II can often impede detection of liver lesions. Following a rationale that FDG accumulates over time in malignant cells as compared to healthy or inflamed hepatocytes, several authors have proposed that PET-CT imaging may improve lesion detectability over time through an improvement in the tumor-to-background ratio
[24,25]. It is known that FDG uptake by a tumor may not plateau before 90–120 minutes and peak levels may persist for up to 4 hours after injection
[26]. Using target-liver ratios, we will investigate whether the 30 minutes delay between both PET-scans contribute to an improved differentiation of post-ablation inflammation and residual tumor
[15]. The study has not been designed to provide semi-quantitative values for FDG uptake as predictors of therapeutic response, generally expressed as the standard uptake volume (SUV). However, the SUV can vary considerably and the time lapse between FDG injection and acquisition is a major contributor to this variation
[27].

Follow-up is only worthwhile when patients comply to a physician’s recommendations, and compliance with medical advice has been a challenge since first described by Hippocrates
[28]. Numerous factors determine whether a person’s behaviour coincides with medical advice, such as the duration of therapy, the complexity of the regimen and psychosocial factors
[29]. Adherence to follow-up can also be affected by a patients’ negative experience of examinations such as discomfort and pain
[30,31]. These patient preferences may contribute to final decision making on follow-up imaging, especially when modalities are known to be equally effective. We formulated the hypothesis that PET-MRI provides a less favourable experience when compared to PET-CT, as the MRI examination may elicit anxiety due to the need to remain immobile and alone while enclosed in the MRI tunnel for a prolonged period of time, in addition to the noise associated with the examination
[32].

In this study, we solely focus on the ability of PET-MRI to identify intrahepatic recurrences, since most recurrences after local treatment of the liver reoccur in the liver

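### The accuracy analysis compares PET-MRI with MRI, CT and PET-CT singly and defines no combined PET-CT plus 4-phase CT result, so a sensitivity gain over PET-CT alone can overstate the gain over current follow-up

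*Protocol article*

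**What the plan says.** **The accuracy comparison.** Statistical analysis: "We will determine the accuracy of PET-MRI for diagnosing recurrent disease compared to each imaging method (MRI, CT and PET-CT". McNemar's test is then applied between PET-MRI and the other modalities. Under Image analysis, every lesion gets its own form for each modality, and "The reviewers will be blinded to the results of the other imaging modalities and to final patient outcome". Table 3 gives positivity criteria for ceCT, MRI and FDG PET. Neither a joint PET-CT plus 4-phase CT read nor a rule for combining the two scores is described.

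**Current practice.**
- Primary and secondary objectives: "all FDG PET-MRI images will be compared to FDG PET-CT and 4-phase liver CT images, which are the current standard of care".
- Study procedure: routine first-year follow-up at the study centre is "three-monthly whole-body FDG PET-CT and 4-phase liver CT".
- Recurrent disease and repeated treatment, on what prompts a review: "If recurrent disease is suspected on either 4-phase CT of the liver or on PET-CT, the patient will be evaluated for re-treatment".
- Abstract, Background: PET-MRI is assessed "as compared to the current standard, FDG PET-CT".

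**What each examination contains.** PET-MRI includes PET, T2, diffusion-weighted and multiphase contrast-enhanced liver MRI. The Imaging text describes a low-dose CT for attenuation and fusion, followed by a diagnostic 4-phase liver CT. Table 2, however, lists the 4-phase CT between the start and the end of the PET-CT session.

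**The concern.** PET-MRI as the index test carries both FDG uptake and contrast-enhanced liver imaging. If PET-CT is read with its low-dose CT only, each comparator carries just one of these: PET-CT has the uptake and 4-phase CT has the contrast phases. A lesion that PET-MRI finds and PET-CT misses may be one that the same patient's 4-phase CT already shows. Such a lesion counts as a gain over PET-CT but is no gain over follow-up in which both scans are done and suspicion on either is acted on.

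What is at stake is the interpretation. The Background hypothesizes that PET-MRI is superior to PET-CT for early detection of new intrahepatic lesions and so can improve decisions. That second step is about what PET-MRI adds to the information clinicians already have, and pairwise comparisons with single modalities do not measure it.

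**Working it through.** **The plan's own figure.** The Sample size calculation gives 88% for finding 5 events with n = 20 and p = 0.35. The exact binomial tail P(X ≥ 5) is 0.8818, so it reproduces. The present point does not depend on it.

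**Inputs.**
- Sensitivity of fused PET-MRI 0.93 and of PET-CT 0.76, cited in the Background.
- Sensitivity of 4-phase CT: not given. Assumed 0.50 to 0.70 for illustration.
- Specificities: not given. Assumed 0.90 for each of PET-CT and 4-phase CT.

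**Sensitivity of the combination.** Let c be the share of lesions missed by PET-CT that 4-phase CT detects. With an either-positive rule:

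combined sensitivity = 0.76 + (1 − 0.76) × c = 0.76 + 0.24c

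gain of PET-MRI over the combination = 0.93 − (0.76 + 0.24c) = 0.17 − 0.24c

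If every CT detection is also a PET-CT detection (nested), c = 0. If errors are independent, c equals the CT sensitivity.

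| c | Combined sensitivity | Gain of PET-MRI |
|---|---|---|
| 0 (nested) | 0.760 | 0.170 |
| 0.2 (partial overlap) | 0.808 | 0.122 |
| 0.5 (independent, CT 50%) | 0.880 | 0.050 |
| 0.6 (independent, CT 60%) | 0.904 | 0.026 |
| 0.7 (independent, CT 70%) | 0.928 | 0.002 |

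Since c cannot be negative, the sensitivity gain over PET-CT alone is never smaller than the gain over the combination.

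**Specificity of the combination.** With independent false positives it is 0.90 × 0.90 = 0.81. If the false positives coincide it is 0.90. The combination is therefore at most as specific as either scan, and a single-modality comparison can understate a specificity advantage of PET-MRI.

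**Scale in this study.** The expected number of patients with LTP is 20 × 0.35 = 7. One patient whose LTP is seen on 4-phase CT but missed on PET-CT changes per-patient sensitivity by 1/7, about 14 points. The choice of comparator can therefore change the observed result visibly, although 7 events cannot resolve differences of this size with precision.

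**The case against.** **PET-CT is the stated comparator.** The abstract names PET-CT as the standard, and the Background hypothesizes that PET-MRI is at least equivalent to PET-CT for LTP. The Discussion adds that repeat treatment is often started on PET-CT alone. This stands: the PET-MRI versus PET-CT comparison answers a question the article poses and should be kept. It does not remove the point. Equivalence to PET-CT alone would not show equivalence to the pair. At equal sensitivity of 0.76, PET-MRI would trail the combination by 0.24c, which is 12 points at c = 0.5.

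**A reader might infer that PET-MRI is never set against the combined standard.** The article does not support that. A secondary outcome compares the treatment a panel would choose on PET-MRI with the treatment received on PET-CT and 4-phase CT. The wording of the primary comparison in the objectives also allows a joint comparison. The treatment-choice outcome concerns management, however, and the Statistical analysis section does not carry the joint reading into accuracy.

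**The low-dose premise is not settled.** Table 2 places the 4-phase CT inside the PET-CT session, so the PET-CT read might include it. If so, much of the concern falls away, but the article would need to say so, because it lists CT and PET-CT as separate methods.

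**The figures are borrowed.** The 93% and 76% come from post hoc fusion with 1.5 Tesla MRI for hepatic metastases, not from lesions after ablation. They serve only as an illustration.

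**The combined rule is a referral trigger.** Suspicion on either scan leads to review by the liver board, with biopsies before repeat ablation, and PET-MRI plays no part in that route. A comparator built on this trigger is tied to the selection of lesions for histology. This is a good reason not to replace the primary comparator outright. The same dependence already affects PET-CT and CT taken singly.

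**Uptake time.** The Discussion discloses that "The period between FDG injection and acquisition of the PET-CT in this study is 30 minutes longer than the standard protocol", and the protocol plans dual-time-point work with target-liver ratios. A reader might want discordant lesions re-scored by uptake time. The planned analysis largely covers this, so nothing is asked for here.

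**Conclusion.** The accuracy analysis as written defines no combined PET-CT plus 4-phase CT result, although three sections treat the pair as current follow-up and the abstract names PET-CT alone. A sensitivity gain over PET-CT can overstate the gain over current practice. On the cited 93% and 76%, the overstatement runs from nothing (nested detections) to nearly all of the 17 points (independent errors, CT sensitivity assumed 70%). The true overlap is unknown from the document.

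A reader might infer that PET-MRI's gain is overstated as a matter of course. The document does not support that: the size of the sensitivity effect is undetermined, and specificity can shift in the opposite direction. Nor does it follow that PET-CT is the wrong primary comparator. What is missing is an added comparison and a consistent definition of the standard. This should be changed before the images are analysed.

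**What to change.** 1. Reconcile the definition of the standard of care across the abstract, the objectives and the Statistical analysis section.
2. State whether the PET-CT read includes the 4-phase liver CT or only the low-dose CT.
3. Add to the Statistical analysis section a prespecified comparison of PET-MRI with the combined result. The combination is positive if either PET-CT or 4-phase CT is scored malignant at that site and visit, using the same score cut-off as the single modalities. It is derived from the forms already collected. Report both sensitivity and specificity.
4. Keep the single-modality comparisons alongside it. Rest any conclusion about gain over current follow-up on the combined comparison, and note that suspicion on these same scans also triggers histological verification.

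The cost is one derived variable and one extra comparison, with no new scans or patients. PET-MRI's sensitivity advantage may look smaller.
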